### Perioperative bleeding

Data on number of transfused units of red blood cell will be collected. The E-CABG bleeding classification has been proposed as a simple classification of perioperative bleeding [20] and it has been shown being comparable to the Universal Definition of Perioperative Bleeding [21] in predicting early mortality [22]. Herein we will adopt a simplified version of the E-CABG perioperative classification. This classification defines severe bleeding as transfusion of more than 4 units of red blood cells during and after surgery and/or reoperation for excessive intrathoracic bleeding (Table 6).

**Table 6 Tab6:** Simplified E-CABG perioperative bleeding classification [20]

Grades	Intervention for treatment of bleeding
0	No RBC transfusion or transfusion of 1 unit of RBCs
1	Transfusion of 2–4 units of RBCs
2	Transfusion of 5–10 units of RBCs and/or reoperation for intrathoracic bleeding
3	Transfusion of > 10 units of RBCs

*RBC* red blood cell

### Reoperation for bleeding

Chest reopening for excessive bleeding. It qualifies as a reoperation for bleeding also any reoperation for excessive bleeding in patients in whom the sternum was left open. Chest reopening for hemodynamic instability without excessive bleeding as well as pericardial/pleural puncture or chest drain insertion for retained blood syndrome do not qualify as reoperations for bleeding.

### Deep sternal wound infection/mediastinitis

Proven infection involving deep sternal wound tissues and/or mediastinum.

### Procedures for vascular complications

Any vascular and endovascular procedure for ischemic or bleeding complications.

These complications will encompass neurologic complications, mesenteric ischemia, upper and lower limb ischemia as well as bleeding from the aorta and its branches.

### Mechanical circulatory support

The use of intra-aortic balloon pump and/or venoarterial extracorporeal membrane oxygenation for postoperative acute heart failure. The duration of treatment of these salvage therapies will be documented.

### Length of stay in the intensive care unit

Overall length of treatment in the intensive care unit, including readmissions, at the institution where surgery for TAAD was performed.

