**Methods:**

Nineteen centers of cardiac surgery from seven European countries have collaborated to create a multicentre observational registry (ERTAAD), which will enroll consecutive patients who underwent surgery for acute TAAD from January 2005 to March 2021. Analysis of the impact of patient’s comorbidities, conditions at referral, surgical strategies and perioperative treatment on the early and late adverse events will be performed. The investigators have developed a classification of the urgency of the procedure based on the severity of preoperative hemodynamic conditions and malperfusion secondary to acute TAAD. The primary clinical outcomes will be in-hospital mortality, late mortality and reoperations on the aorta. Secondary outcomes will be stroke, acute kidney injury, surgical site infection, reoperation for bleeding, blood transfusion and length of stay in the intensive care unit.

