## Background

Acute Stanford type A aortic dissection (TAAD) is a life-threatening condition. Surgery is usually performed as a salvage procedure and is associated with increased postoperative early mortality and morbidity [1]. Although early mortality has declined during the last years [2], the recent The Nordic Consortium for Acute Type A Aortic Dissection registry including 1189 patients operated from 2005 to 2015 in 8 centers showed that 30-day mortality after surgery for acute TAAD was as high as 18% [3]. The multicentre, prospective German Registry for Acute Aortic Dissection type A including 2137 TAAD patients operated from 2006 and 2010 documented a 30-day mortality of 16.9% [4]. A more recent analysis of the Society of Thoracic Surgeon database including 7353 patients operated from 2014 and 2017 for acute TAAD reported a 30-day mortality of 17% [5]. Furthermore, surgery for TAAD is often complicated by major adverse events such as stroke [5] and acute kidney failure [6], which may have a significant impact on late survival. In this scenario of significant postoperative mortality and morbidity, surgeon faces the controversial issue of the extent of surgical repair for acute TAAD by avoiding a major surgical repair, which may increase the risk of early adverse events, and by resecting segments of the aorta which otherwise may expose the patient to the risk of late aortic-related complications [7, 8]. Understanding the balance between the patient’s conditions which may not allow extensive procedure and those treatment strategies which may limit the risk of late adverse events in patients who remain alive long after the surgery is essential for an appropriate management of TAAD. However, previous registries [1, 3] did not provide information on the long-term durability of these procedures. We have planned the multicenter European registry of surgery for acute TAAD (ERTAAD) to evaluate the contemporary early outcomes and the durability of different surgical strategies for acute TAAD at 15 years in a large study population.

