## Methods

The ERTAAD is an observational registry including patients who underwent surgery for acute TAAD at 19 centers of cardiac surgery located in seven European countries (Belgium, Czech Republic, Finland, France, Germany, Italy and the United Kingdom) (Table 1) from January 1, 2005 to March 31, 2021. Data will be retrospectively collected on patients treated during the study period and the aim is to gather further data for future clinical research on this topic. Data on consecutive patients with acute TAAD will be collected into a Microsoft Access datasheet (Redmond, Washington, USA) with pre-specified baseline, operative and outcome variables. Permission to conduct this study will be requested from institutional or national review boards according to local legislation.

**Table 1 Tab1:** Participating centers

Participating centers	
1. Ziekenhuis Oost-Limburg, Genk, Belgium	
2. Saint-Luc’s Hospital, Brussels, Belgium	
3. Sint-Jan Hospital, Bruges, Belgium	
4. Antwerp University Hospital, Edegem, Belgium	
5. University Hospitals Leuven, Leuven, Belgium	
6. Institute of Clinical and Experimental Medicine, Prague, Czech Republic	
7. Helsinki University Hospital, Helsinki, Finland	
8. Jean Minjoz University Hospital, Besançon, France	
9. Hôpital Henri Mondor, Assistance Publique - Hôpitaux de Paris, Créteil, France	
10. Leipzig Heart Center, Leipzig, Germany	
11. University Heart and Vascular Centre Hamburg, Hamburg, Germany	
12. Münster University Hospital, Münster, Germany	
13. University of Turin, Turin, Italy	
14. University of Verona Medical School, Verona, Italy	
15. University of Udine, Udine, Italy	
16. Glenfield Hospital, University Hospitals of Leicester, Leicester, UK	
17. Liverpool Heart and Chest Hospital, Liverpool, UK	
18. Sheffield Teaching Hospital, Sheffield, UK	
19. Southampton University Hospital, Southampton, UK	

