## Outcomes and their definition criteria

### Hospital death

All-cause death having occurred during the index hospitalization, i.e. at the institution where surgery for TAAD was performed.

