## Statistical analysis

Statistical analyses will be conducted using Stata v. 15.1 (StataCorp LLC, Texas, USA) and SPSS v. 27.0 (IBM Corporation, Armonk, NY, USA) statistical softwares. Continuous variables and outcomes will be reported as mean and standard deviation as well as median and interquartile range. Categorical variables and outcomes will be reported as counts and percentages. A *p* < 0.05 will be set for statistical significance. Differences between the study groups will be evaluated using the Fisher’s exact test, the Chi-square test, the linear-by-linear association test, the Mann-Whitney test and the Kruskall-Wallis test. The McNemar test and paired samples T-test will be used in the paired groups. Propensity score matching will be performed to balance treatment strategies for baseline differences. A propensity score will be estimated using a non-parsimonious multilevel mixed-effects logistic regression considering the cluster effect of the participating centers whose results may be affected by the referral pathway, surgical techniques and perioperative care. Multilevel mixed-effects logistic regression model will include all available baseline variables. The estimated propensity score will be employed for inverse propensity score weighting analysis and one-to-one propensity score matching analysis using a caliper width of 0.1 to 0.2 of the standard deviation of the estimated logit. Standardized differences < 0.10 will be considered an acceptable imbalance between the matched cohorts.

Survival analysis will be performed using the Kaplan-Meier method with the log-rank test and the Cox proportional hazards method. Competing risk analysis with the Gray’s test will be performed for late non-fatal adverse events because patient’s death might hinder the observation of these events. Regression models will include covariates with *p* < 0.05 or *p* < 0.2 in univariate analysis according to the number of covariates of interest. Risk estimates will reported as hazard ratios and subdistribution hazard ratios with their 95% confidence intervals.

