Logistic and linear regression analyses will be employed to identify independent risk factors for early adverse events with and without a stepwise approach. For the purpose of developing a risk scoring method from this registry, the study cohort will be randomly divided into two datasets, i.e. the derivation data set (75.0% of patients) and the validation data set (25.0% of patients). Univariate analysis will be performed on all candidate covariates of the derivation dataset to identify predictors of in-hospital mortality. Multiple logistic regression analysis will be then performed using the derivation dataset. A stepwise procedure with a bootstrap approach will be used, and 100 samples will be extracted with a size of 70% of the derivation dataset. A stepwise procedure will be applied to each sample (probability to stay = 0.05; probability to entry = 0.1). Variables selected in at least 50% of the stepwise procedures will be included in the regression model. Additional covariates were selected using a forward selection comparing the Akaike information criterion for the models with and without each covariate. The model with the lowest Akaike information criterion will be selected for each forward step, until the inclusion of a new covariate determined an increase in the Akaike information criterion value. The model will be tested in the validation data set for calibration, using the Hosmer–Lemeshow test, and for discrimination using the receiver-operating characteristic curve analysis. A comparison of the predictive ability of the new score with the current risk scoring methods for prediction of in-hospital mortality will be performed in the overall dataset as well as in the validation dataset using the DeLong test. The improvement of discrimination of the new score will be estimated by calculating the net reclassification index and the integrated discrimination improvement. Finally, to evaluate the adaptability of the new score for prediction of late mortality, Kaplan–Meier curves stratified by deciles of the new score will be plotted.

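### ICU length of stay has no rule for patients who die, so as printed it mixes survivors' recovery with the timing of death

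*Protocol article*

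**What the plan says.** All references are to the protocol article.

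- **Status.** The abstract's Methods paragraph names ICU stay last among the secondary outcomes: "Secondary outcomes will be stroke, acute kidney injury, surgical site infection, reoperation for bleeding, blood transfusion and length of stay in the intensive care unit".
- **Definition.** The section on length of stay in the intensive care unit reads "Overall length of treatment in the intensive care unit, including readmissions, at the institution where surgery for TAAD was performed". It settles readmissions and institution, but not patients who die.
- **Population.** The Methods section states "Data on consecutive patients with acute TAAD will be collected". No section limits ICU stay to survivors.
- **Death.** Hospital death is a separate outcome, "All-cause death having occurred during the index hospitalization", and is not combined with ICU stay.
- **Analysis.** The Statistical analysis section names the Mann-Whitney and Kruskal-Wallis tests for group differences and the paired t-test for matched groups. For early outcomes it says "Logistic and linear regression analyses will be employed to identify independent risk factors for early adverse events with and without a stepwise approach". Its only provision for death as an obstacle is "Competing risk analysis with the Gray’s test will be performed for late non-fatal adverse events because patient’s death might hinder the observation of these events".
- **Expected mortality.** The Background cites 30-day mortality of 18%, 16.9% and 17% from three registries.

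**The concern.** Fewer ICU days are naturally taken as a better result. A patient who dies in theatre or on the first day has almost no ICU time, so one of the worst courses scores as one of the best. A patient who dies after weeks in intensive care scores as one of the slowest recoveries. Without a rule for deaths, the outcome combines how fast survivors recover, how many patients die, and when they die.

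This matters for the contrasts the registry is built for. The Sample size calculation section makes total arch repair against more limited resection a main topic, for early as well as late outcomes. The Background says that major repair may raise the risk of early adverse events. The urgency classes extend to patients resuscitated before bypass. Where early mortality differs, a difference in ICU days cannot be attributed to recovery.

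**Working it through.** The plan gives no effect size, power or sample size for ICU stay, so there is no figure of its own to reproduce. The check asks when, and how far, counting deaths at their observed ICU time misleads.

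**Inputs from the document.** Mortality of 17% in the reference group (Background). Significance at p < 0.05 (Statistical analysis). About 5% total arch repair and more than 6000 patients expected (Sample size calculation): 0.05 × 6000 = 300, so one-to-one matching would give about 300 pairs.

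**Assumptions, not in the document.** Survivors' ICU stay is lognormal with median 5 days and log SD 0.9, the same in both groups. ICU time of patients who die is lognormal with median m and log SD 1.0, with m varied from 1 to 10 days. Mortality in the comparison group B is 27%.

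**Direction.** Let p_A and p_B be the mortality in the two groups, and θ the probability that a patient who dies has a shorter ICU time than a survivor. Summing over the four combinations of death and survival in a random pair, the terms reduce to

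P(B shorter) = 0.5 + (p_B − p_A)(θ − 0.5), with θ = Φ[ln(5/m) / √(0.9² + 1.0²)].

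For m = 2: ln(2.5) = 0.916; 0.916/1.345 = 0.681; θ = 0.752; P(B shorter) = 0.5 + 0.10 × 0.252 = 0.525. If deaths are ranked worst, θ = 0 and P(B better) = 0.5 − 0.10 × 0.5 = 0.45, whatever m is.

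**Means.** A lognormal mean is median × exp(SD²/2): survivors 5 × exp(0.405) = 7.50 days; deaths, for m = 2, 2 × exp(0.5) = 3.30 days. Group A: 0.83 × 7.50 + 0.17 × 3.30 = 6.8. Group B: 0.73 × 7.50 + 0.27 × 3.30 = 6.4.

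**Test behaviour.** Simulated with 300 per group (4,000 runs for Mann-Whitney, 8,000 for the paired t-test with randomly formed pairs). The nominal rate of significance in one direction is 2.5%.

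| Median ICU time of deaths (days) | P(B shorter) | Mean A, B (days) | Median A, B (days) | Mann-Whitney favours B | Paired t favours B |
|---|---|---|---|---|---|
| 1 | 0.538 | 6.5, 5.9 | 4.1, 3.6 | 38% | 15% |
| 2 | 0.525 | 6.8, 6.4 | 4.4, 4.0 | 17% | 10% |
| 3.5 | 0.510 | 7.2, 7.0 | 4.7, 4.6 | 6% | 4% |
| 5 | 0.500 | 7.6, 7.7 | 5.0, 5.0 | 2% | 2% |
| 10 | 0.480 | 9.0, 9.9 | 5.5, 5.9 | 0.2% | 0.2% |

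In the 2-day row, repeated simulations with fewer runs gave 18% to 21% for Mann-Whitney. In the 10-day row, Mann-Whitney instead finds a significantly longer stay in B in 13% of runs. In an unmatched comparison of 300 against 5700, it favours B in about 62%, 33% and 10% of runs for m = 1, 2 and 3.5. With mortality 17% against 22% and 300 per group, the figures are 13%, 7% and 4%.

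**The case against.** The strongest reply is that this is a condensed article, the analysis plan is not shown, and a death rule for one secondary duration is the kind of detail left to it. The definition does not say that deaths are included, and no analysis sentence names ICU stay. In-hospital mortality is a primary outcome reported alongside, so a more lethal strategy would be visible. Total ICU days is also a legitimate measure of resource use.

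Part of this stands. Inclusion of deaths is an inference from an unrestricted definition applied to consecutive patients. The mortality result beside it limits the harm, and raw ICU days remain valid as resource use. But the article does print its analysis methods. It recognises that death can prevent an outcome from being observed, and confines that provision to late non-fatal events. An early duration falls outside it and is left to methods that take observed days at face value.

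Two stronger readings are tempting. A reader might infer that a strategy with more early deaths will necessarily show a shorter ICU stay. The document does not support this: it gives no timing of death, and the bias disappears or reverses if deaths come as late as survivors' discharge or later. A reader might also infer that the scale is reversed for about one patient in six. That fraction is 30-day mortality, which includes deaths after a long ICU stay or after ICU discharge. The share with a truncated stay is unknown.

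**Conclusion.** The point holds in a limited form. As printed, ICU stay has no rule for deaths, and the named methods would count a death at its truncated time. Groups that differ in early mortality therefore cannot be compared on recovery.

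The size depends on the assumed ICU time of patients who die. For a ten-point mortality difference and 300 per group, wrongful significance in favour of the more lethal group ranges from about 38% down to the nominal 2.5% as that median goes from 1 to 5 days; beyond that the error runs the other way. In the 2-day case the shift is about 0.4 days in both mean and median. The survivor distribution and the 27% mortality are also assumptions.

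This is worth changing but not critical: the outcome is secondary and mortality is reported next to it. The uncertain sign is no reassurance, because a reader of the result could not tell which way it had been pushed.

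**What to change.** State how deaths are handled. Either option below would do:

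1. Analyse time from surgery to final ICU discharge alive at the operating institution, with death as a competing event, and report the cumulative incidence of discharge alive. This extends to an early outcome the method already planned for late events. Taking the final discharge keeps the readmissions that the definition counts.
2. Keep ICU days, but rank in-hospital deaths as the worst outcome in the rank tests.

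In either case, report raw ICU days in survivors as description only, since survivors are a group selected after treatment.

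The cost is mainly wording. ICU stay and hospital death are already collected, but option 1 needs the dates of ICU discharge and death, which should be confirmed as available in retrospective records. The effect is also no longer a simple difference in days. ICU-free days to day 30, and a rule for transfers to another hospital's ICU, are possible only if dated ICU stays and discharge destination are recorded. The present definition stops at the operating institution, so this cannot be assumed.

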### Late outcomes

Data on patient’s survival status will be collected. Patients lost to follow-up will be reported.

Data on any repeat surgical or endovascular procedure on the aorta will be reported along with its urgency, indications and aortic segment treated.

## Sample size calculation

The impact of total aortic arch repair compared to more limited aortic resection on the early and late outcomes will be one of the main topics of research from this registry. Therefore, in the light of the expected limited frequency of this surgical strategy, we performed a sample size analysis considering the extent of distal aortic resection. Despite the limitation of a pooled analysis which did not take in to account the cumulative incidences from competing risk analysis and the segment of repeat operation, Poon et al. [23] estimated a pooled hazard ratio on 0.73 (95%CI 0.56–1.18) of freedom from any late aortic reoperation for total arch replacement. Based on this hazard ratio, a sample size of 163 patients per study groups would be enough to reject the null hypothesis (alpha 0.05, power 0.80). Pan et al. [24] reported a freedom from distal reoperation after ascending aortic resection at 8 years of 95.3% which was not statistically different from that of hemiarch or total aortic arch repair (92.4%, *p* = 0.22). For the sample size calculation of a non-inferiority trial, we assumed a freedom rate from distal aortic reoperation of 95% and we considered that a difference in the reoperation rate as large as 10% in favor of a total aortic arch repair still allow the less extensive repair to be non-inferior (delta = 0.1, power 0.90, one-sided confidence 97.5%), the required sample size would be 100 patients per each group. We assume that about 5% of patients have undergone total arch repair in this collaborative registry and therefore a study population of 4000 patients would be enough to investigate the impact of total aortic arch repair in preventing late aortic reoperation in patients with acute TAAD. The participating hospitals are expected to provide a sample size of more than 6000 patients (i.e. at least a mean of > 20 procedures for acute TAAD each year), which would prevent a type II error.

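### The hazard ratio of 0.73 behind the total-arch sample size does not fit the 95% CI of 0.56–1.18 printed beside it, so this input cannot be verified as printed

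*Protocol article*

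**What the plan says.** The section "Sample size calculation" of the protocol article makes the effect of total arch repair on late aortic reoperation one of the registry's main topics. For the superiority question it takes its effect size from a cited pooled analysis, which it says "estimated a pooled hazard ratio on 0.73 (95%CI 0.56–1.18) of freedom from any late aortic reoperation for total arch replacement". It then states that "a sample size of 163 patients per study groups would be enough to reject the null hypothesis", with "alpha 0.05, power 0.80". Whether alpha is one- or two-sided is not stated.

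The same section adds that "We assume that about 5% of patients have undergone total arch repair in this collaborative registry" and concludes that 4000 patients would be enough, with more than 6000 expected. It says that this number would prevent a type II error, and the Strengths section repeats the reassurance in milder form.

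The article does not explain why the interval is asymmetric around 0.73, and it gives no second value for this hazard ratio elsewhere.

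**The concern.** Confidence intervals for hazard ratios are normally built on the log scale, so the point estimate should be the geometric mean of the two limits. Here the upper limit is much further from 0.73 than the lower one, even on the log scale. That points to a misprint or a transcription error in at least one of the three numbers.

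This matters because 0.73 is the only effect size behind the superiority calculation, and reoperation on the aorta is one of the primary outcomes. If 0.73 is the wrong figure, the target effect is weaker and the stated requirement is too small. If a limit is wrong, the plan misreports the strength of its own premise. For example, it would show a result as compatible with no effect when the source interval excluded 1.

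**Working it through.** **Inputs**, all from "Sample size calculation": HR 0.73; 95% CI 0.56 to 1.18; alpha 0.05; power 0.80; 163 per group (326 in total); about 5% total arch repair; 4000 to 6000 patients.

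**1. Reproducing the plan's figure.** With equal groups, two-sided alpha 0.05 and 80% power, (1.960 + 0.842)² = 7.849.
- Schoenfeld: 4 × 7.849 / (ln 0.73)² = 31.40 / 0.0990 = 317 events, or 159 per group.
- Freedman: 7.849 × (1.73/0.27)² = 323 events after rounding up, or 162 per group.

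Both are within 3% of 163. One-sided alpha gives 125 to 127 per group and does not fit. So 0.73 is the value that was used, and 163 matches a number of events per group.

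**2. Checking the interval on the log scale.**
- Estimate to lower limit: ln(0.73/0.56) = 0.265, implied standard error 0.265/1.96 = 0.135.
- Estimate to upper limit: ln(1.18/0.73) = 0.480, implied standard error 0.480/1.96 = 0.245.
- Ratio of the two distances: 1.81. It should be about 1.
- Geometric midpoint: √(0.56 × 1.18) = 0.813. With limits rounded to two decimals it can range from √(0.555 × 1.175) = 0.808 to √(0.565 × 1.185) = 0.818.
- The arithmetic midpoint, (0.56 + 1.18)/2 = 0.87, does not give 0.73 either.

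**3. What each single misprint would imply.**
- 0.56 and 1.18 right: HR about 0.81.
- 0.73 and 0.56 right: upper limit 0.73²/0.56 = 0.95 (0.93 to 0.97 with rounding).
- 0.73 and 1.18 right: lower limit 0.73²/1.18 = 0.45 (0.44 to 0.46 with rounding).

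**4. Consequence if the point estimate is the wrong figure.** At the unrounded midpoint (0.8129), Schoenfeld gives 31.40 / 0.0429 = 732 events and Freedman 737, against 317 and 323 at 0.73. The ratio is 732/317 = 2.3. On the plan's own counting, 732/2 = 366 per group. The plan's 5% implies 0.05 × 4000 = 200 to 0.05 × 6000 = 300 total-arch patients. That covers 163 but not 366.

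**5. What the 326 delivers.** Power is Φ(|ln HR| × √events / 2 − 1.96).
- If 326 were events: 81% at HR 0.73 and 46% at HR 0.813.
- The plan says patients. Suppose freedom from reoperation with limited repair is 95%. This is an assumption: the section uses 95% for distal reoperation, in its non-inferiority calculation. Freedom with total arch repair is then 0.95^0.73 = 0.963 and the mean event proportion 0.0434, so 326 patients yield about 14 events. Power at HR 0.73 is about 9%.
- With an assumed 80% freedom, the same steps give about 57 events and 22% power at HR 0.73.

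**The case against.** The strongest counter-case has four parts.

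- **Which figure is wrong is unknown.** If either limit is the misprint, 0.73 and the calculation built on it are unaffected. Only one of the three single-misprint cases harms the sizing. This stands. A reader might infer that 0.73 is itself wrong, or that 0.81 should replace it; the document supports neither.
- **The interval method is not visible.** A cited pooled analysis could have used a method that gives an asymmetric interval. This is less likely, and the article mentions no such method, but it cannot be excluded. The finding therefore carries the log-scale assumption openly.
- **The fall from 81% to 46% is not the plan's power.** A reader might take it as the loss this error causes. It holds only for 326 events, whereas the plan counts patients. On the assumptions above, power at HR 0.73 is already about 9% to 22%. Counting events as patients is a separate and larger problem in the same sentence, and correcting the hazard ratio or its interval would not restore 80%.
- **The practical reach is limited.** Enrolment is fixed by centres and calendar period. The non-inferiority calculation of 100 per group does not use this hazard ratio. The section already concedes a limitation of the pooled analysis, and the analysis section promises hazard ratios with confidence intervals, so an imprecise null result would be visible. All of this stands. It confines the damage to the stated justification for the sample size, but it does not make the three printed numbers agree.

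**Conclusion.** The inconsistency is real and rounding does not explain it. Assuming the usual log-scale interval, at least one of 0.73, 0.56 and 1.18 is wrong. The document does not identify which, so the effect size behind the 163 per group and 80% power is unverified as printed, rather than shown to be false.

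The effect on the sizing depends on the source check. It is nil for the HR input if a limit is wrong. If the point estimate is wrong, the required number of events rises about 2.3-fold, and the total-arch group of 200 to 300 patients falls short even on the plan's own counting.

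In every case the unqualified claim of sufficiency goes too far. The interval as printed includes 1. Even with an upper limit corrected to about 0.95, it would reach effects much weaker than 0.73.

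**What to change.** 1. Check the hazard ratio and both limits against the cited pooled analysis and correct whichever is wrong. If the source interval is genuinely asymmetric, say so and name the method.
2. If the point estimate changes, recompute the requirement from the corrected value and compare it with the expected 200 to 300 total-arch patients. If only a limit changes, correct it and keep 0.73 as the input.
3. In either case, qualify the statement that the sample is enough to reject the null hypothesis: make it conditional on the assumed hazard ratio and say how uncertain that value is.
4. Base any restated power on the expected number of reoperations, not on the number of patients, and do not present 81% or 46% as the plan's power.

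The cost is one source check and a few lines of recalculation. No extra patients or data are needed, though the restated power may be less favourable.

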### Strengths

This registry will include detailed data on patients’ characteristics, operative strategies and outcomes from centers with large volume of cardiac surgery and significant experience in the treatment of acute and chronic aortic diseases. This may reduce the risk of bias related to limited experience in the surgical treatment of aortic diseases. This multicenter registry will allow recruiting of more than 6000 patients, which is expected to decrease the risk of type II errors. The long follow-up of this study will allow reliable analysis of the durability of different surgical repair strategies.

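### The 163 patients per group quoted for a hazard ratio of 0.73 is the number of reoperation events needed per group, so the stated 80% power is not delivered

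*Protocol article*

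**What the plan says.** The Sample size calculation section names total arch repair against more limited resection as a main research topic and gives two calculations for it.

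- **Hazard ratio.** A pooled analysis "estimated a pooled hazard ratio on 0.73 (95%CI 0.56–1.18) of freedom from any late aortic reoperation for total arch replacement". From this the article concludes that "a sample size of 163 patients per study groups would be enough to reject the null hypothesis (alpha 0.05, power 0.80". No event rate, follow-up time or censoring is given for this figure.
- **Non-inferiority.** A second study "reported a freedom from distal reoperation after ascending aortic resection at 8 years of 95.3"%, against 92.4% for hemiarch or total arch repair. Assuming 95% freedom from distal reoperation, a margin of 0.10, power 0.90 and one-sided 97.5% confidence, the article obtains 100 per group.

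It then assumes that about 5% of patients had total arch repair and concludes that "a study population of 4000 patients would be enough to investigate the impact of total aortic arch repair in preventing late aortic reoperation". Finally it expects more than 6000 patients, "which would prevent a type II error".

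**The concern.** A log-rank or Cox comparison gains its power from events, and late aortic reoperation is uncommon in every figure that the article quotes. A requirement of 163 patients per group for a hazard ratio as modest as 0.73 is therefore implausibly small, and it is close to the usual event count for that hazard ratio.

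The figure carries weight. It is one of the two numbers that 5% of 4000 = 200 total arch patients is meant to cover, and the statement about type II error follows from that. Aortic reoperation is a primary outcome in the abstract. If the superiority comparison is in fact poorly powered, a non-significant result could be read as showing no durability benefit when the likelier explanation is too few events.

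**Working it through.** **Inputs from the Sample size calculation section:** HR 0.73, read as the hazard of reoperation with total arch against limited repair; alpha 0.05; power 0.80; total arch share 5%; 4000 and 6000 patients; distal reoperation 4.7% and 7.6% at 8 years, and 5% assumed. Sidedness is not stated. Two-sided alpha reproduces the figure; one-sided gives 125 to 127 per group and does not.

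**Step 1. Reproduce 163.** With (1.960 + 0.842)² = 7.849 and (ln 0.73)² = 0.0990:

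- Schoenfeld, 1:1: 4 × 7.849 / 0.0990 = 317 events, 158.5 per group.
- Freedman, 1:1: (1.73 / 0.27)² × 7.849 = 322.2, so 323 events, 161.5 per group.
- Exponential hazards, no censoring: [1.960 × √(2 × 0.865²) + 0.842 × √(1 + 0.73²)]² / 0.27² = 162.3, so 163 per group.

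The last formula gives the printed number exactly, and it assumes that every patient has the event. With 326 events, power is 80% (Freedman) to 81% (Schoenfeld).

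**Step 2. Power with 163 patients per group.** Let e be the proportion reoperated after limited repair. The total arch proportion is 1 − (1 − e)^0.73. Expected events are D = 163 × [e + 1 − (1 − e)^0.73], and power = Φ(√D / 2 × 0.3147 − 1.960).

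| e | Events | Power |
|---|---|---|
| 5% | 14 | 9% |
| 7.6% | 21 | 11% |
| 15% | 43 | 18% |
| 30% | 86 | 31% |
| 50% | 146 | 48% |

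At e = 5%, 80% power would need about 3,655 (Schoenfeld) to 3,724 (Freedman) patients per group.

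**Step 3. Whole registry at a 5:95 split.** Events needed: 7.849 / (0.05 × 0.95 × 0.0990) ≈ 1,668. Expected events: D = N × [0.95e + 0.05 × (1 − (1 − e)^0.73)]. Power = Φ(√(D × 0.0475) × 0.3147 − 1.960). The detectable HR is the value at which this power reaches 80%, with D recomputed for that HR.

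| e | 4000: events, power | Detectable HR | 6000: events, power | Detectable HR |
|---|---|---|---|---|
| 5% | 197, 16% | 0.40 | 296, 22% | 0.47 |
| 7.6% | 300, 22% | 0.47 | 450, 31% | 0.54 |
| 15% | 592, 39% | 0.59 | 889, 53% | 0.65 |

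For HR 0.73, power reaches 80% at e ≈ 28% with 6000 patients and e ≈ 42% with 4000.

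**Step 4. One-to-one matched sets**, which the Statistical analysis section plans. If every total arch patient is matched there are 200 pairs (4000) or 300 pairs (6000). Power is 10% to 12% at e = 5%, 12% to 17% at 7.6%, and 21% to 29% at 15%.

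**Step 5. Non-inferiority calculation.** (1.960 + 1.282)² × 2 × 0.95 × 0.05 / 0.10² = 99.8, so 100 per group. This reproduces.

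**Step 6. Quoted interval.** On the log scale, 0.56 to 1.18 centres on √(0.56 × 1.18) = 0.81, not 0.73. A point estimate of 0.73 with lower limit 0.56 would imply an upper limit of 0.73² / 0.56 = 0.95.

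**The case against.** Several points on the other side are fair.

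- **The endpoints differ.** The hazard ratio is for any aortic reoperation, while every rate in the article is for distal reoperation. This stands: the rate of any reoperation is not given and may be higher, so the whole-registry shortfall cannot be fixed at one value. It does not rescue the 163, which has only 48% power even if half of the limited-repair group is reoperated.
- **There is a second calculation.** This also stands. A reader might infer that the whole sample size section collapses, but the non-inferiority figure is right on its inputs and 200 total arch patients cover it nominally. It shows that limited repair is not worse by more than 10 percentage points; it does not support detecting that total arch repair prevents reoperation.
- **The registry's size is set by its dates, and results will carry confidence intervals.** True. No analysis changes, and intervals limit misreading. The printed power is still wrong.

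Two stronger readings are tempting. One is that the 15-year durability aim is unattainable because surgery dates run to March 2021. The article gives no closing date for follow-up, and staggered entry is handled by the planned survival methods, so this cannot be concluded. The other is that the Strengths section repeats the error. It says only that the size "which is expected to decrease the risk of type II errors", which is true of any larger sample.

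**Conclusion.** The concern holds for the hazard ratio calculation. The 163 is an event requirement per group printed as patients; taken as patients, it gives about 9% to 11% power at 5% to 7.6% reoperation, not 80%. At those rates 4000 patients give 16% to 22% and 6000 give 22% to 31%, so the statement that the expected size would exclude a type II error is unsupported for this comparison.

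The 163-per-group result needs only the stated hazard ratio, alpha and power. The registry powers also rest on the 5% total arch share and on borrowing distal rates as a range for any reoperation. They assume proportional hazards and leave out centre effects, competing deaths, loss to follow-up and losses from matching or weighting; the last three would lower power further.

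The asymmetric interval is a secondary query. A reader might infer that the true pooled estimate is 0.81, but the article cannot show whether the estimate or a limit is misprinted.

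**What to change.** In the Sample size calculation section:

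1. Replace the 163-per-group sentence with an event requirement: about 317 to 323 events at 1:1, or about 1,668 at a 5:95 split, for HR 0.73 at two-sided alpha 0.05 and 80% power.
2. Report power or detectable hazard ratio for 4000 and 6000 patients over a stated range of any-aortic-reoperation rates, for the full cohort and for the matched sets.
3. Limit the conclusion that 4000 patients are enough to the non-inferiority question.
4. Delete the clause on preventing a type II error.
5. Check the hazard ratio and its interval against the cited pooled analysis.

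The cost is the rewording of one paragraph and a less favourable power statement. No additional patients and no change to the analyses are needed.
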